## 3. Quality Evaluation

### 3.1 Patient Compliance and Withdrawal

Establish a good relationship with subjects, provide health consultation, explain the benefits of participating in the experiment, and minimize dropouts or withdrawals during the study.

### 3.2 Protocol Deviation

Strictly adhere to the protocol approved by the Ethics Committee. Once the researcher identifies any protocol deviation, it should be immediately documented and explained. After review and confirmation by the principal investigator, the information should be submitted to the monitor/sponsor.

### 3.3 Evaluation

**Efficacy Assessment:** Evaluate treatment effects by conducting statistical analysis of data collected before and after the intervention.

#### Safety Assessment

**3.3.1 Baseline Signs and Symptoms:** Before inclusion in the study, subjects undergo comprehensive inquiry and physical examination. The inclusion and exclusion criteria are strictly followed to ensure subject safety.

**3.3.2 Laboratory Safety Assessment:** The evaluations in this experiment can be

completed in the ward or outpatient treatment hall. In case of emergencies, timely responses are ensured.

3.3.3 Physical Examination and Vital Signs: All participants in the experiment are medical staff, and subjects must be in good condition during participation. The experiment is conducted within the hospital (ward, outpatient treatment hall). In case of emergencies, medical staff will perform physical examinations and measure vital signs for the subjects.

### 3.4 Adverse Event Reporting

#### 3.4.1 Adverse Events

Adverse events include: ① Skin tingling sensation in the electrical stimulation area: The patient's experience will be recorded, along with their tolerance level. Generally, the tingling sensation gradually diminishes or disappears after stimulation. If the patient cannot tolerate it, they will withdraw from the experiment. ② Fatigue: Fatigue may occur during exercise therapy or functional assessments. Subjects will be given timely rest, and fatigue levels will be recorded. Fatigue typically alleviates after rest. Throughout the experiment, dedicated medical staff will accompany the patient to ensure their safety as much as possible.

3.4.2 Definition of Adverse Events: Harmful reactions unrelated to the experimental objectives that occur during the normal intervention process.

3.4.3 Severity Assessment: Adverse reactions are categorized into levels 1–5 based on severity:

- Level 1: Mild; asymptomatic or extremely mild symptoms; detectable only through tests; no intervention required.
- Level 2: Moderate; requires minor or non-invasive local intervention; decline in instrumental activities of daily living scale scores.
- Level 3: Severe or clinically significant but not immediately life-threatening; requires hospitalization or extended hospital stay; disability; decline in physical self-care ability

scale scores.

- Level 4: Life-threatening; requires urgent intervention.

- Level 5: Death due to adverse reaction.

3.4.4 Correlation Judgment: Harmful reactions unrelated to the experimental objectives that occur during the experiment, such as skin tingling during electrical stimulation, fatigue during exercise training or functional assessments, or falls, are considered adverse reactions related to this experiment.

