### **2.2 Study Participants**

**2.2.1 Sample Size Estimation:** Based on preliminary trial results, using the sample size calculation formula for comparing means between two independent samples, with the primary outcome measure (FMA-LE score) expected effect size  $d=0.8$ ,  $\alpha=0.05$

(two-tailed), and power  $1-\beta=0.8$ , an estimated 26 participants per group is required. Considering an approximate 10% dropout rate, 29 participants per group are planned, totaling 58 participants.

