#### 2.3.2 Transcutaneous Auricular Vagus Nerve Stimulation Protocol

Device and Parameters: A Transcutaneous Auricular Vagus Nerve Stimulator will be used.

Real stimulation parameters are set as: frequency 25Hz, pulse width 250-500 $\mu$ s, using an intermittent stimulation mode (e.g., 30 seconds on, 30 seconds off). Intensity is adjusted to a level where the patient feels a distinct but non-painful tingling sensation (typically 2-3mA below the perception threshold).

Stimulation Site: Electrodes are attached to the left concha area (distribution area of the auricular branch of the vagus nerve).

Sham Stimulation Setup: The device appearance, electrode placement location, and operational procedure are identical to the real stimulation group. However, the stimulator delivers an ineffective, very low-intensity current that is barely perceptible (e.g., <0.1mA) to mimic device operation.

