## 2.4 Outcome Measures

Assessments will be conducted by professional rehabilitation therapists blinded to group allocation at baseline (pre-intervention) and immediately after the 6-week intervention period.

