### 2.4.1 Primary Outcome Measure:

1. Lower Limb Motor Function: Assessed using the Fugl-Meyer Assessment for Lower Extremities.

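### Withdrawing patients who cannot tolerate the tingling may cost primary outcomes mainly in the real-stimulation arm

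*Protocol*

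**What the plan says.** Protocol section 3.4.1 lists tingling at the stimulation site as the first adverse event and sets the rule: "If the patient cannot tolerate it, they will withdraw from the experiment". 

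Section 2.3.2 describes the two arms. For real stimulation, "Intensity is adjusted to a level where the patient feels a distinct but non-painful tingling sensation". For sham, "the stimulator delivers an ineffective, very low-intensity current that is barely perceptible (e.g., <0.1mA) to mimic device operation". The real-arm sentence also carries a parenthesis, "typically 2-3mA below the perception threshold", which does not fit with a sensation that the patient distinctly feels.

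Section 2.4 places the assessments "at baseline (pre-intervention) and immediately after the 6-week intervention period", and section 2.4.1 makes the Fugl-Meyer lower-extremity score (FMA-LE) the primary outcome. 

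Section 2.2.1 requires 26 per group and then adds a margin: "Considering an approximate 10% dropout rate, 29 participants per group are planned". Section 3.1 asks only that dropouts be kept to a minimum. No section provides for assessing a patient after withdrawal.

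**The concern.** The rule in section 3.4.1 does not separate two different events: stopping the stimulation and leaving the study. As worded, the first brings about the second. With only one assessment after baseline, a patient who leaves before week 6 contributes no FMA-LE.

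The trigger is an effect of the randomised treatment. If one arm is meant to feel the current distinctly and the other barely at all, intolerance of the sensation arises mainly in one arm. The real-arm result would then come from patients who tolerated stimulation, with no matching selection among controls. Randomisation does not protect that comparison, and outcomes that were never collected cannot be recovered by analysis.

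**Working it through.** **1. The plan's own figure.** Inputs from section 2.2.1: d = 0.8, two-sided alpha 0.05, power 0.80. The two-sample t-test solution is 25.52 per group, rounded up to 26. With 10% dropout, 26/0.9 = 28.9, rounded up to 29, or 58 in total. The stated sample size reproduces.

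**2. Does one-sided loss cost power?** The allowance is 29 − 26 = 3 per group, or 6 in the trial. Power of the t-test at d = 0.8:

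| Real arm | Control arm | Power |
|---|---|---|
| 29 | 29 | 0.849 |
| 26 | 29 | 0.828 |
| 23 | 29 | 0.802 |

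Even if the whole allowance fell in the real arm, power would stay at 0.80. The issue is bias, not power.

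**3. Size of the bias (illustration).** Assumptions, none of them in the documents:
- m of the 29 real-arm patients withdraw for intolerance, with m = 3 (10% of that arm) or m = 6 (the whole trial's allowance in one arm).
- Their mean outcome would have been δ SD below the mean of the full real arm, with δ = 0.5 or 1.
- The control arm is held at 29 for simplicity, and the comparison uses only patients with a week-6 value.

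The full-arm mean is the weighted average of those who leave and those who stay, so the completers' mean lies above it by

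b = m × δ / (29 − m).

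For m = 3 and δ = 1, b = 3/26 = 0.115. For m = 6 and δ = 1, b = 6/23 = 0.261.

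The chance of a significant two-sided result when there is no true effect follows from the noncentral t distribution with noncentrality b / √(1/(29 − m) + 1/29) and 56 − m + 0 degrees of freedom, that is (29 − m) + 29 − 2. For m = 6 and δ = 1 the noncentrality is 0.261/0.279 = 0.93 on 50 degrees of freedom.

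| m | δ | Shift b (SD) | Share of d = 0.8 | Type I error |
|---|---|---|---|---|
| 3 | 0.5 | 0.058 | 7% | 0.055 |
| 3 | 1 | 0.115 | 14% | 0.070 |
| 6 | 0.5 | 0.130 | 16% | 0.074 |
| 6 | 1 | 0.261 | 33% | 0.150 |

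**4. Sensitivity to the definition.** If the gap is measured from the completers instead of the full arm, the shift is m × δ / 29. That gives 0.05 to 0.10 SD with 3 withdrawals and 0.10 to 0.21 SD with 6. The type I error is then 0.054 to 0.066 and 0.065 to 0.112.

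**5. Direction.** If those who withdraw would have done better than the rest of their arm, each shift changes sign and works against taVNS.

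**The case against.** *Few patients may be affected.* Intensity is adjusted individually to a non-painful level, and section 3.4.1 expects the sensation to fade after stimulation. This stands as a limit on size. The protocol nevertheless foresees intolerance and fixes what follows from it.

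*The asymmetry depends on contested wording.* If real stimulation were delivered below the perception threshold, as the parenthesis in section 2.3.2 says, there would be little tingling in either arm and little asymmetry. This stands too. Section 3.4.1 lists tingling as an expected event, which supports the other reading, but the two wordings must be reconciled.

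*The statistical analysis plan may deal with it.* Analysis sets and the handling of missing data may well be set out there, and their absence from the protocol is no fault. The point concerns data collection, which that plan cannot repair afterwards.

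*Stronger readings that the documents do not support.* A reader might infer that the control arm would be complete. It need not be: the 10% allowance applies to both groups, and controls may leave for other reasons. A reader might also infer that withdrawn patients are excluded from the primary comparison by rule. Section 2.6 names tests but no analysis set. Nor does section 2.2.1 say that intolerance withdrawals are what its dropout allowance counts. Finally, a type I error of about 15% belongs only to the most extreme assumed case. The other three cases lie between 0.055 and 0.074, and no figure in the documents links skin tolerance to FMA-LE.

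**Conclusion.** The point holds as an avoidable risk of treatment-related missing outcomes, not as a demonstrated bias. Followed as written, the rule loses the primary outcome of every patient who cannot tolerate the tingling before week 6, and mainly in the real arm if the distinct-tingling wording governs. The planned allowance covers the loss of numbers but not the selection.

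Under the assumptions shown, the effect is modest at the planned dropout rate and becomes material only in the upper scenario. Both the frequency of withdrawal and the prognosis of those who leave are unknown, and so is the direction of any bias. The change is worth making because it is cheap and must precede the loss of data.

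**What to change.** Reword section 3.4.1 so that stopping stimulation for intolerance is distinct from leaving the study. State that the week-6 FMA-LE, Functional Ambulation Classification and gait assessment are sought from every randomised patient unless consent to follow-up is withdrawn. Record and report stops for intolerance by arm. Reconcile the two intensity statements in section 2.3.2; which of them is right is for the investigators to settle. When stimulation stops remains a clinical decision and is not touched by this change.

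The cost is a change of wording and attendance at a visit that is already scheduled, with no new patients or instruments. The downside is that the estimate will include some partly exposed patients.

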## 2.5 Safety Monitoring

Any adverse events occurring during the study period, such as skin irritation, dizziness, discomfort, or falls, will be recorded and analyzed for their relationship to the interventions.

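### The adverse-event rules in section 3.4 conflict with sections 2.5 and 2.3.2: relatedness is declared by rule, the intended tingling is a listed adverse event, and the collection window varies

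*Protocol*

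**What the plan says.** Protocol section 2.5 covers "Any adverse events occurring during the study period, such as skin irritation, dizziness, discomfort, or falls", and says that these "will be recorded and analyzed for their relationship to the interventions".

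Section 3.4 gives further rules:

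- Section 3.4.1 opens its list of adverse events with "Skin tingling sensation in the electrical stimulation area: The patient's experience will be recorded, along with their tolerance level". It sets no intensity or tolerance level below which tingling is not an adverse event. Its second item is fatigue, in exercise therapy or in functional assessments.
- Section 3.4.2 defines an adverse event as "Harmful reactions unrelated to the experimental objectives that occur during the normal intervention process".
- Section 3.4.4 takes "Harmful reactions unrelated to the experimental objectives that occur during the experiment, such as skin tingling during electrical stimulation", adds fatigue and falls as further examples, and states that these "are considered adverse reactions related to this experiment".

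Section 2.3.2 adjusts active stimulation to a level where "the patient feels a distinct but non-painful tingling sensation". The same sentence adds in parentheses that this typically lies 2–3 mA below the perception threshold. Sham current is described as barely perceptible, for example under 0.1 mA.

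**The concern.** Adverse-event records are this trial's evidence on the harms of a combined treatment that section 1 presents as new. Three features of section 3.4 weaken that evidence.

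First, relatedness is settled by rule in section 3.4.4 and by analysis in section 2.5. Falls are named in both places and handled differently. Section 1 says these patients have balance deficits and a raised fall risk, so some falls will occur in both arms whatever the stimulation does. A rule that calls them all related cannot separate those from falls caused by treatment.

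Second, the sensation sought in one arm is a listed adverse event, and sham is designed to produce little of it. A difference between the arms in such a count would partly reflect the set-up procedure.

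Third, the window is described in three ways, so two members of staff could classify the same event differently.

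**Working it through.** The protocol gives no adverse-event figure to reproduce. The only number needed is the arm size in section 2.2.1. For d = 0.8, two-sided α = 0.05 and power 0.80, the t-test solution is 25.52, so 26 per group. With 10% dropout, 26 / 0.9 = 28.9, so 29 per group and 58 in total. The plan's figures reproduce.

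**Relatedness.** Sections 3.4.2 and 3.4.4 describe their classes in almost the same words: harmful reactions unrelated to the objectives. Section 3.4.4 has the wider window (the experiment rather than the normal intervention process). So an event that meets the definition in 3.4.2 also falls in the class that 3.4.4 deems related. Under the literal rule there is no remaining group of unrelated events, and the analysis in section 2.5 has nothing to decide. The verdict is also given for the experiment as a whole. Under section 2.3 both arms receive the exercise and only the stimulation differs, so the rule does not address the attribution that matters for comparing arms.

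**Tingling.** Tingling is the target in section 2.3.2, an adverse event in 3.4.1 and a related adverse reaction in 3.4.4. The severity scale in 3.4.3 does not screen it out, because its lowest level admits extremely mild symptoms that need no intervention.

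The effect on an any-adverse-event proportion can be written down. Let b be the proportion with some other adverse event, equal in both arms, and let t_A and t_S be the proportions reporting tingling on active and sham. If tingling is independent of other events:

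- Active: 1 − (1 − b)(1 − t_A)
- Sham: 1 − (1 − b)(1 − t_S)
- Difference: (1 − b)(t_A − t_S)

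The protocol gives none of these quantities. I assume b = 5% to 30%.

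| t_A − t_S (assumed) | Difference, b = 30% | Difference, b = 5% | Patients out of 29 |
|---|---|---|---|
| 0 points | 0 | 0 | 0 |
| 10 points | 0.70 × 10 = 7.0 points | 0.95 × 10 = 9.5 points | 2.0 to 2.8 |
| 50 points | 0.70 × 50 = 35 points | 0.95 × 50 = 47.5 points | 10.2 to 13.8 |

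With intended tingling left out, the difference is zero on the same assumptions. The same holds for related events, since 3.4.4 names tingling as related.

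**Window.** Section 2.5 uses the study period, 3.4.2 the normal intervention process, and 3.4.4 the experiment. The formal definition has the wording that can be read most narrowly, and it also asks for a reaction. Because section 2.5 speaks of adverse events, a reader who applies 3.4.2 strictly could leave out an event that 2.5 appears to want.

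**The case against.** The strongest reply is that section 2.5 still stands. Nothing says that section 3.4.4 overrides it, and relation to the experiment, which includes assessments, is not plainly the same question as relation to the interventions. That is fair as far as it goes: staff could do both. But the section on relationship judgement is 3.4.4, it names falls as section 2.5 does, and it offers no route to an unrelated verdict. The two need reconciling.

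On tingling, one can say that 3.4.2 requires harm, that the target in 2.3.2 is non-painful, and that tolerance is recorded, so tolerated tingling might not count. This shows ambiguity, but 3.4.1 lists tingling without such a condition. The parenthesis in 2.3.2 does stand as an objection to any fixed size, because it leaves unclear how many active patients feel tingling.

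Some stronger readings are tempting, and the documents do not support them:

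- A reader might infer that events between treatment sessions, and so most of follow-up, are dropped. No section limits events to sessions. The intervention process can mean the six weeks, 3.4.4 says the experiment, and 3.4.1 counts fatigue in assessments.
- A reader might infer that every active patient has an adverse event by construction. The parenthesis in 2.3.2 prevents that conclusion.
- A reader might infer that the whole safety comparison is invalid. No between-arm comparison of adverse events is named; only counts that include intended tingling, or rest on the relatedness rule, are affected.
- A reader might infer that the record would unblind the assessors. Nothing says that they see it.

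**Conclusion.** Wrong as written, of moderate severity. Two conflicts are plain from the text: the blanket relatedness rule in 3.4.4 against the analysis in 2.5, and the listing of tingling in 3.4.1 and 3.4.4 against its role as the target in 2.3.2. The third, the differing windows, is an ambiguity: 3.4.2 can be read more narrowly than 2.5 but does not clearly exclude anything.

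Followed literally, relatedness carries no information, and counts of all or related events are raised in the active arm to the extent that tingling is commoner there. The amount cannot be fixed from the protocol. It is zero if tingling is equally common in both arms, and 7 to 9.5 percentage points for each 10-point difference under the assumed 5–30% of other events and independence. The sample size, primary outcome and efficacy analysis are untouched.

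**What to change.** - **Section 3.4.2:** align the definition and window with section 2.5, as any untoward event in the study period, whether or not related, and use that one window throughout section 3.4.
- **Section 3.4.4:** replace the blanket rule with a case-by-case judgement of relationship. Preferably state whether the relation is to stimulation or to exercise, since only stimulation differs between arms. Section 2.5 does not itself promise that split, so it is an addition.
- **Section 3.4.1:** record tingling at the intended level as a stimulation-sensation item, separate from adverse events, and report adverse events by arm with and without it.
- **Section 2.3.2:** the felt-tingling target and the parenthesis placing intensity below the perception threshold contradict each other and must be reconciled by the sponsor. Until then the intended level in the item above is undefined.

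The cost is a few sentences, one case-report-form item and slightly more event recording. The changes belong before data collection, because event class and causality are hard to reconstruct afterwards.

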#### **4. Ethics**

##### **4.1 Ethics Committee**

Submit a detailed research plan and related materials to the Ethics Committee.

##### **4.2 Patient Information and Informed Consent**

Patient information will be kept strictly confidential. Files will be stored in locked cabinets and accessible only to researchers. Government regulatory authorities or members of the Ethics Review Committee may review your personal data at the research unit as required by regulations. No patient information will be disclosed in the publication of research results. Before participating in the experiment, patients must sign an informed consent form.
